# The effect of low- versus normal-pressure pneumoperitoneum during laparoscopic colorectal surgery on the early quality of recovery with perioperative care according to the enhanced recovery principles (RECOVER): study protocol for a randomized controlled study

**DOI:** 10.1186/s13063-020-04496-8

**Published:** 2020-06-17

**Keywords:** Pneumoperitoneum, Intra-abdominal pressure, Deep neuromuscular block, Laparoscopy, Colorectal, Laparoscopic surgery, Quality of recovery, Rocuronium, Sugammadex

## Abstract

**Background:**

There is increasing evidence for the use of lower insufflation pressures during laparoscopic surgery. Deep neuromuscular blockade allows for a safe reduction in intra-abdominal pressure without compromising the quality of the surgical field. While there is considerable evidence to support superior surgical conditions during deep neuromuscular blockade, there is only a limited amount of studies investigating patient outcomes. Moreover, results are not always consistent between studies and vary between different types of laparoscopic surgery. This study will investigate the effect of low-pressure pneumoperitoneum facilitated by deep NMB on quality of recovery after laparoscopic colorectal surgery.

**Methods:**

The RECOVER study is a multicenter double-blinded randomized controlled trial consisting of 204 patients who will be randomized in a 1:1 fashion to group A, low-pressure pneumoperitoneum (8 mmHg) facilitated by deep neuromuscular blockade (post tetanic count of 1–2), or group B, normal-pressure pneumoperitoneum (12 mmHg) with moderate neuromuscular blockade (train-of-four response of 1–2). The primary outcome is quality of recovery on postoperative day 1, quantified by the Quality of Recovery-40 questionnaire.

**Discussion:**

Few studies have investigated the effect of lower insufflation pressures facilitated by deep neuromuscular blockade on patient outcomes after laparoscopic colorectal procedures. This study will identify whether low pressure pneumoperitoneum and deep neuromuscular blockade will enhance recovery after colorectal laparoscopic surgery and, moreover, if this could be a valuable addition to the Enhanced Recovery After Surgery guidelines.

**Trial registration:**

EudraCT 2018-001485-42. Registered on April 9, 2018. Clinicaltrials.govNCT03608436. Registered on July 30, 2018.

## Background

There is increasing evidence for the use of lower insufflation pressures during laparoscopic surgery [1–5]. Consensus guidelines recommend using the lowest intra-abdominal pressure with an adequate view of the surgical field [6, 7]. This level varies between patients based on many factors that influence compliance of the abdominal wall. Deep neuromuscular blockade (NMB) allows for a safe reduction in intra-abdominal pressure without compromising the quality of the surgical field. Our research group has performed multiple studies investigating surgical conditions in living kidney donors. In a randomized controlled trial in laparoscopic donor nephrectomy patients, we show that compared to moderate NMB, deep NMB allows for lower mean insufflation pressures while maintaining significantly better surgical conditions on the Leiden-Surgical Rating Scale (L-SRS, displayed in Table 1) [9]. Similar results have been reported for surgical conditions during other abdominal laparoscopic procedures. Meta-analysis shows that compared to moderate NMB, deep NMB improves laparoscopic surgical space conditions with a mean difference of 0.65 (95% CI 0.47–0.83) on the L-SRS scale [10]. While there is considerable evidence to support superior surgical conditions during deep NMB, only a limited amount of studies investigate patient outcomes. Moreover, results are not always consistent between studies. Understandably, results can vary between different types of laparoscopic surgery. As carefully outlined by Fuchs-Buder and colleagues in their review, the location of the surgical field (e.g., is the space confined, encompassed by muscular tissue or close to the diaphragm) will have a great influence on the effect of lower pneumoperitoneum pressures or deep neuromuscular block on surgical conditions [11]. A systematic review by Madsen et al. provides evidence for the use of deep NMB during laparoscopic cholecystectomy, prostatectomy, and nephrectomy [12]. Results of Torensma et al. support deep NMB during laparoscopic bariatric surgery [13]. Only a few studies have investigated the influence of lower intra-abdominal pressure or deep NMB on surgical conditions and patient outcomes for colorectal laparoscopic surgery. Koo et al. found less abrupt increases in intra-abdominal pressure with deep NMB as compared to moderate NMB [14]. Cho and colleagues found decreasing intra-abdominal pressure during laparoscopic colorectal surgery provides no cardiopulmonary benefits, regardless of the level of NMB [15]. Diaz-Cambronero et al. used an individualized strategy to titrate intra-abdominal pressure and found 78% of colorectal surgeries could be completed at low pressure (8 mmhg) [16]. Kim et al. found that compared to moderate NMB, deep NMB allows titration to lower insufflation pressures (9.3 mmHg versus 12 mmHg) while maintaining the surgical field. Additionally, they report lower postoperative pain scores, a lower incidence of postoperative shoulder tip pain and faster recovery of bowel function in the deep NMB group [17]. Whether low pressure pneumoperitoneum and deep NMB improve early quality of recovery after laparoscopic colorectal surgery is still unknown. We hypothesize low pressure pneumoperitoneum facilitated by deep NMB will enhance postoperative quality of recovery.

**Table 1 Tab1:** Leiden-Surgical Rating Scale [8]

	Scale	Description
1	Extremely poor conditions	The surgeon is unable to work due to coughing or due to the inability to obtain a visible laparoscopic field because of inadequate muscle relaxation. Additional muscle relaxants must be given.
2	Poor conditions	There is a visible laparoscopic field but the surgeon is severely hampered by inadequate muscle relaxation with continuous muscle contractions and/or movements with the hazard of tissue damage. Additional muscle relaxants must be given.
3	Acceptable conditions	There is a wide visible laparoscopic field but muscle contractions and/or movements occur regularly causing some interference with the surgeon’s work. There is the need for additional muscle relaxants to prevent deterioration.
4	Good conditions	There is a wide laparoscopic working field with sporadic muscle contractions and/or movements. There is no immediate need for additional muscle relaxants unless there is the fear for deterioration.
5	Optimal conditions	There is a wide visible laparoscopic working field without any movement or contractions. There is no need for additional muscle relaxants.

## Methods

The RECOVER study is a multicenter single-blinded randomized controlled trial that will be performed at three general teaching hospitals in the Netherlands. A list of participating centers is provided at the trial registration site (clinicaltrials.gov, NCT03608436). We aim to assess the effect of a lower pressure pneumoperitoneum facilitated by deep neuromuscular blockade on quality of recovery in patients undergoing laparoscopic colorectal surgery. All eligible patients will be screened and asked for informed consent. A flow chart of the inclusion process is shown in Fig. 1. Please see Additional files 1 and 2 for the SPIRIT figure and checklist, respectively.

**Fig. 1 Fig1:**
[figure not shown]
Study flow chart

### Study population

We aim to include 204 patients undergoing elective laparoscopic colorectal surgery. Adult individuals (≥ 18 years old) scheduled for laparoscopic colorectal surgery with a primary colonic anastomosis are eligible for this study. Patients will be excluded if they meet any of the following exclusion criteria: insufficient control of the Dutch language to understand patient information and fill out the questionnaires, primary colostomy, neo-adjuvant chemotherapy, chronic use of analgesics or psychotropic drugs, use of NSAIDs in the 5 days before surgery, known or suspected allergy to rocuronium or sugammadex, neuromuscular disease, indication for rapid sequence induction, severe liver or renal disease (creatinine clearance < 30 ml/min), morbid obesity (a body mass index > 35 kg/m^2^), or a deficiency of vitamin K-dependent clotting factors or coagulopathy, as sugammadex may increase the risk of bleeding in this group. Patients with a primary colostomy are not included in the study because this is likely associated with a significantly altered recovery process. Patients who have received neo-adjuvant chemotherapy are excluded because a substudy investigating immune function will be performed in a subgroup of the participants. Details of the substudy will not be further discussed here.

### Study protocol

After obtaining informed consent, patients will be randomized in a 1:1 fashion to group A, low-pressure pneumoperitoneum (8 mmHg) facilitated by deep neuromuscular blockade defined as a post tetanic count (PTC) of 1–2, or group B, normal-pressure pneumoperitoneum (12 mmHg) with moderate neuromuscular blockade defined as a train-of-four (TOF) count of 1–2. Randomization is supported by our statistician and will be performed by a randomization list created with Sealed Envelope [18]. Stratification by center and surgical technique (laparoscopic or robot assisted) will be used. Upon hospital admission and before surgery, patients will complete baseline questionnaires: the validated Dutch versions of the Quality of Recovery-40 [19] (QoR-40), McGill pain [20], and RAND-36 [21] questionnaires. In the participating hospitals, perioperative care is structured following the Enhanced Recovery After Surgery (ERAS) society guidelines for elective colorectal surgery [22, 23]. Adherence to the key elements of these guidelines will be scored for all patients.

In the operating room, the surgical team (surgeons and OR nurses) is blinded to the intervention allocation. The anesthesiologist and anesthesiologist assistant are not blinded in order to adequately monitor and regulate patient vitals and the level of neuromuscular blockade. A non-blinded physician researcher is present to oversee optimal execution of the study protocol. A standardized anesthesia protocol is used for all patients. General anesthesia will be induced with total intravenous anesthesia (TIVA) consisting of propofol 1–3 mg/kg and remifentanil 0.25–2 mcg/kg/min. After initiation of neuromuscular monitoring with the TofScan (an Equip Medikey [24] neuromuscular monitor using acceleromyography), an intubation dose of 0.6 mg/kg rocuronium (rocuroniumbromide, brand name Esmeron) is administered in both groups. After tracheal intubation, all patients are ventilated with pressure regulated volume controlled ventilation with a mixture of oxygen in air (ratio 1:3), 5 cm H_2_0 PEEP, and a tidal volume of 6–8 ml/kg. Respiratory rate is adjusted to reach an end-tidal carbon dioxide between 31 and 43 mmHg. Infusion of intravenous fluids is kept to a minimum, and losses will be replaced. If possible, the use of drains is avoided. When a nasogastric tube is indicated for gastric decompression, it will be removed before the end of surgery. Core temperature is continuously monitored and if necessary modified with a bair hugger temperature system, aiming at 36–37 °C.

General anesthesia is maintained with propofol aimed at a bispectral index score of 45–55, remifentanil 0.25–2 mcg/kg/min, a bolus injection of 0.2–1 mg/kg esketamine and a bolus injection of 1–1.5 mg/kg lidocaine 1% followed by continuous infusion of lidocaine 1% at 0.5–3 mg/kg/h. In both groups, the Automated TOF PTC (ATP) function of the TOF scan is used to measure the level of neuromuscular blockade every 5 min throughout the whole surgery. This function automatically determines whether a response to train-of-four stimulation is present and if TOF count or PTC should be measured. In group A (low pressure PNP with deep NMB), continuous infusion of 0.3–0.4 mg/kg rocuronium is initiated directly after intubation and titrated to a PTC of 1–2. If PTC is 0, continuous infusion will be decreased (but not stopped) until a PTC of 1 or 2 is reached. In group B (normal pressure with moderate NMB), a bolus or low dose of continuous rocuronium can be administered after intubation as normally done in clinical practice, titrating towards a TOF count of 1–2. Reaching deep NMB is carefully prevented in this group; if TOF count reaches 0, the infusion of rocuronium will be stopped until neuromuscular function is recovered.

After introduction of the camera trocar, the insufflation pressure of carbon dioxide is set to 8 mmHg in group A and 12 mmHg in group B, out of the surgical team’s sight. After introduction of the last trocar and every 15 min during surgery, a blinded OR nurse will ask the surgeon to rate the surgical conditions on the Leiden-Surgical Rating Scale (L-SRS) as displayed in Table 1. In case of inadequate surgical conditions (at any time during the surgery), defined as < 4 out of 5 points on the L-SRS scale, intra-abdominal pressure will be increased with 2 mmHg to 10 mmHg and a maximum of 12 mmHg in group A or 14 mmHg and a maximum of 16 mmHg in group B, respectively. If the level of NMB is not in the desired range, this will be corrected first. If surgical conditions remain compromised despite the increase in pressure, the surgeon can decide to convert to a hand-assisted or open procedure. All administered medication and intraoperative parameters are documented in the digital anesthesia report in the electronic patient file as in usual clinical practice. At the end of surgery, intraoperative complications will be registered by the surgeon.

After skin closure, NMB is reversed using sugammadex (natriumsugammadex, brand name Bridion), 4 mg/kg in group A and 2 mg/kg in group B, unless the TOF ratio in group B has spontaneously recovered to > 0.9. Extubation is performed when TOF ratio is stable at > 0.9 for 2 min and patients are fully awake. Postoperative pain management consists of acetaminophen and patient-controlled intravenous analgesia (PCIA) morphine or oxycodone in both groups.

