Intraoperative secondary outcome measures are quality of the surgical field quantified on the L-SRS every 15 min, estimated blood loss, pulmonary mean driving pressure, and intraoperative complications. Table 2 shows an overview of questionnaires and parameters collected at the post anesthesia care unit (PACU), surgical ward, and after discharge. Postoperative secondary outcomes are quality of recovery measured with the QoR-40 questionnaire after 72 h and 1 week; pain scores; postoperative nausea and vomiting (PONV); use of analgesics and anti-emetics after 1, 8, 24, and 72 h; intra-operative and postoperative complications up to 3 months after surgery (classified by the CLASS-Intra [25] and Clavien-Dindo [26] classifications, respectively); and length of hospital stay and time to reach discharge criteria. If patients are discharged before completion of the QoR-40 after 72 h or 1 week, the questionnaires are taken home and returned to the researchers by post. Pain is scored on a scale of 0–10 in rest and upon movement, if pain is acceptable yes or no and if shoulder pain is present yes or no. Nausea is scored on a scale of 0–10. Discharge criteria are as follows: adequate pain relief with oral analgesics, passage of flatus or defecation, intake of solid foods is tolerated, patient is capable of independent mobilization, and patient accepts discharge. The actual date of hospital discharge is also registered. Pain, nausea, and discharge criteria are scored by the ward nurse responsible for the clinical care of the patient, who is also blinded to the treatment allocation. Postoperative complications are extracted from the electronic patient file 1 month after surgery.

**Table 2 Tab2:** Variables and time points

	− 1 day	1 h	8 h	24 h	48 h	72 h	1 week	1 month	3 months

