### Statistical methods and sample size calculation

The mean clinically important difference on the QoR-40 questionnaire as described by Myles et al. is 6.3 points on a scale of 40–200, with a standard deviation of 15 points [32]. In order to achieve 80% power to detect a 6.3 point difference with an *α* of 5%, a sample size of 89 patients per group is needed. Considering a 15% conversion rate to open surgery, 204 patients are required to secure 178 patients for the final analysis.

For the primary outcome analysis, factorial ANCOVA will be used to compare the QoR-40 score on postoperative day 1 for groups A and B and adjusted for covariates. For secondary outcome variables, a Student’s *t* test will be used to compare normally distributed variables, and a Mann-Whitney *U* test will be used for skewed variables. For categorical variables, a chi-square test will be performed. A *P* value of < 0.05 will be considered statistically significant. All analyses will be performed on an intention to treat base. For exploratory outcome measures, Bonferroni correction for capitalization on chance will be applied.

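### The surgeon-rated L-SRS is compared with an unadjusted two-sample test, which is valid but leaves any between-surgeon, center and technique variation in the error

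*Protocol article*

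**What the plan says.** All references are to the protocol article.

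- **Who rates.** Study protocol: after the last trocar and every 15 minutes, "a blinded OR nurse will ask the surgeon to rate the surgical conditions on the Leiden-Surgical Rating Scale (L-SRS". No rater common to all cases is described.
- **Where.** Methods: the trial "will be performed at three general teaching hospitals in the Netherlands".
- **Status.** Outcome measures: "Intraoperative secondary outcome measures are quality of the surgical field quantified on the L-SRS every 15 min". It is secondary and has no power target.
- **Randomization.** Study protocol: "Stratification by center and surgical technique (laparoscopic or robot assisted) will be used". Surgeon is not a stratification factor.
- **Analysis.** Statistical methods and sample size calculation: for secondary outcomes a Student's t "test will be used to compare normally distributed variables", and a Mann-Whitney U "test will be used for skewed variables". Adjustment appears only for the primary outcome, where "factorial ANCOVA will be used to compare the QoR-40 score on postoperative day 1 for groups A and B and adjusted for covariates". The significance rule is that a P "value of < 0.05 will be considered statistically significant".

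**The concern.** For this outcome the surgeon is the measuring instrument. Table 1 gives each L-SRS level a written description, but the levels still turn on judgment: how often contractions occur, how far they interfere, whether deterioration is to be feared. If one surgeon habitually scores higher than another, a pooled two-sample test counts that habit as noise. The same holds for differences between hospitals and between laparoscopic and robot-assisted surgery, although randomization is stratified on both.

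What is at stake is precision on one secondary outcome. It is a relevant one, because the rationale in the Background is that deep block allows lower pressure without a worse surgical field, and the L-SRS is the direct measure of that. An interval wider than it need be makes the result harder to read. Neither bias nor a false-positive problem follows.

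**Working it through.** **1. The plan's own figure.** The only sample size stated is for the QoR-40: difference 6.3, SD 15, 80% power, alpha 5% (two-sided assumed).

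n = 2 × (1.960 + 0.842)² × (15/6.3)² = 2 × 7.85 × 5.67 = 89 per group, as stated.

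The standardized difference is 6.3/15 = 0.42 SD. No power is stated for the L-SRS. I use 89 per group for it as well.

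**2. Upper bound on the gain.** Let ρ be the share of the variance of the per-patient L-SRS that lies between surgeons (assumed; the document gives none). The unadjusted variance is 1/(1 − ρ) times the within-surgeon variance. The smallest difference detectable with 80% power is:

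- unadjusted: 2.80 × √(2/89) = 0.42 SD;
- surgeon removed: 0.42 × √(1 − ρ) SD.

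| ρ | Detectable difference (SD) | Power at 0.42 SD |
|---|---|---|
| unadjusted | 0.42 | 80.0% |
| 0.1 | 0.40 | 84.0% |
| 0.2 | 0.38 | 87.9% |
| 0.3 | 0.35 | 91.8% |
| 0.4 | 0.33 | 95.1% |

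This is optimistic, because it treats the surgeon effects as known and the scores as normal.

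**3. Simulation.** Assumed: 178 patients, 12 surgeons, allocation balanced within three centers, normal scores, effect 0.42 SD, surgeon as a fixed effect, 4,000 runs per setting (simulation error about √(0.8 × 0.2/4000) = 0.6 points).

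| ρ | t test | Mann-Whitney | Surgeon in model |
|---|---|---|---|
| 0.1 | 79.6% | 77.0% | 80.6% |
| 0.2 | 80.0% | 78.4% | 85.5% |
| 0.3 | 81.8% | 79.4% | 90.4% |
| 0.4 | 80.9% | 78.6% | 93.8% |

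With no true difference, all three rejected in 4% to 6% of runs. So the planned tests are valid, and at ρ = 0.1 the gain over the t test is 80.6 − 79.6 = 1.0 point, against 4.0 by the formula.

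A second simulation, also with 89 per group and 12 assumed surgeons, covered both normal scores and five-point scores limited by a ceiling. For effects of 0.35 to 0.42 SD the gains were roughly 1-3 points at ρ = 0.1, 4-6 at 0.2 and 12-18 at 0.4. With no between-surgeon variance, a fixed surgeon effect lost about 2-4 points.

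**4. At the L-SRS difference that the article cites.** The Background gives 0.65 points (95% CI 0.47 to 0.83) for deep against moderate block. Power by the formula, 89 per group, SD assumed:

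| Difference | SD | Unadjusted | Adjusted, ρ 0.1 to 0.4 |
|---|---|---|---|
| 0.65 | 1.0 | 99.1% | 99.6% to 99.99% |
| 0.65 | 1.2 | 95.1% | 96.8% to 99.7% |
| 0.65 | 1.5 | 82.4% | 86.2% to 96.2% |
| 0.47 | 1.2 | 74.3% | 78.6% to 92.1% |

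At 0.65 points and an SD of 1.2 or less, at most 4.6 points remain to be gained (99.7 − 95.1), even by the optimistic formula.

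**The case against.** The strongest objection is that nothing here is an error. The test is standard and valid, the outcome is secondary and unpowered, and one generic sentence in a condensed article covers all secondary variables. A rater effect for one of them could well be left to an analysis plan. Part of this stands: the way the 15-minute ratings are summarized is properly left to the fuller document. But the article does name the tests, and it confines adjustment to the primary outcome. That is a stated choice, and it can be improved.

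It is also fair that the size rests wholly on assumptions, and that at the cited 0.65 points the unadjusted test already does well for an SD up to 1.2. Against that, 0.65 compares depths of block alone. Here group A also starts at a lower pressure, and a rating below 4 triggers correction of the block or more pressure in either arm. Both could narrow the difference, though the document does not establish that they do.

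Three stronger readings are tempting and not supported:

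- *That the trial may miss harm to the field and declare equivalence.* No equivalence claim is planned for the L-SRS, and taking a non-significant result as equivalence is an error that rater adjustment would not cure.
- *That adjustment is free because patients are randomized within surgeons.* Stratification is by center and technique only, so balance within surgeon is not guaranteed. Nor does the article say that the operating surgeon is fixed before allocation, or that one surgeon rates a whole case.
- *That the loss is known to be large.* Nothing in the document shows large differences between these raters, who are blinded and work from written descriptors.

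**Conclusion.** The point holds as a minor matter of efficiency. The planned comparison is valid but leaves variation between surgeons, centers and techniques in the error. For a difference of 0.35 to 0.42 SD with 89 per group, modeling the surgeon is worth about 1-3 points of power at a 10% between-surgeon share, 4-6 at 20% and 12-18 at 40%. It is worth little if the difference is near 0.65 points and the SD is at most 1.2. The shares, the SD, the effect in SD units and the 12 surgeons are all assumptions. The primary outcome, its sample size and the type I error are untouched.

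**What to change.** For the L-SRS, replace the t or Mann-Whitney test with a linear mixed model of the per-patient summary score: treatment, center and surgical technique as fixed effects, operating surgeon as a random intercept. Report the treatment difference with its 95% confidence interval, so that precision is visible whatever the P value.

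A random intercept is preferable to a rank test stratified by surgeon, because surgeons with few cases form small strata that lose information.

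The cost is a sentence of analysis text, a few degrees of freedom, and a slight loss of power if surgeons in fact rate alike. The operating surgeon must also be recorded for each case, which the article does not say is done. No change to the design or sample size is needed.
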